**Conclusions:**

RADAR Epilepsy aims at developing a framework of continuous data collection intended to identify ictal and preictal states through the use of aRMT and pRMT in the real-life environment. The study was specifically designed to evaluate the clinical usefulness of the data collected via new technologies and compliance, technology acceptability, and usability for patients. These are key aspects to successful adoption and implementation of RMT as a new way to measure and manage long-term disorders.

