We will develop an analysis strategy for managing multi-sensor data. To this end, we will investigate what type of features derived from the pRMT and aRMT correlate with seizure occurrence and frequency per unit of time (eg, day and week). Seizure occurrence and frequency will be derived from the multiparametric wearable system and from seizure diaries and analyzed separately. Data obtained from wearable biosensors will be used to derive information about participants’ activity during the day and information about sleep and mood. Aggregated features obtained from biosensors, smartphones, and cognitive tests and from ESM and their changes from baseline or previous time points (delta features) will be used for statistical analysis. First, we will use a univariate approach, where the number of seizures per unit of time will be modeled with each variable or feature as a fixed effect and participant as a random effect. Demographics and other baseline characteristics will be added to the model when necessary. Correction for multiple comparisons will be taken into account. Second, using aggregated data obtained through some time duration to predict the number of seizures per the same time duration, we will construct predictive models. Under the assumption that data are missing at random, multiple imputation will be applied for covariates, where missingness is not drastically high. Multivariate prediction models will be constructed, and variable selection, based on, for example, least absolute shrinkage and selection operator L1-regularization for linear models, or different feature selection algorithms will be applied. Model performance will be characterized through cross-validation, putting stress on the sensitivity and specificity of the predictive model.

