In the general epilepsy population, psychiatric comorbidities are frequent, up to 90% identify the presence of at least one seizure precipitant and many report feelings preceding their seizures, including mood, behavior, and cognitive alterations (premonitory features) [53-55]. The presence of complex interactions between seizure precipitants and premonitory features [56,57] makes the assessment of their real impact on seizure risk variation difficult. In addition, studies performed so far are lacking methodological tools that allow an objective and adequate assessment of precipitants, including a measurement of their sudden variation. In fact, irrespective of their retrospective or prospective design, research studies have surveyed patients with the use of cross-sectional questionnaires and diaries, which are subject to recall bias and lack of time stamps. Another major methodological issue of the current literature data is related to the choice of arbitrary time windows between the assessment of a specific factor and the consequent occurrence of a seizure, usually using the data collected the day before to speculate about their influence on seizures occurring the following day. Prediction might be more robust over short time frames for some precipitants and premonitory features and over long time periods for others. Moreover, it is not clear whether a single report of a status (eg, stress or anxiety) reflects the average over the course of a day [58], and multiple collection points per day might be necessary to take into account symptom fluctuations and variations from day to day or moment to moment.

A complete assessment of seizure occurrence, precipitants, premonitory features, and their interactions cannot leave aside all the aforementioned considerations. RADAR Epilepsy aims to overcome the current methodological issues and to develop an ideal framework of continuous data collection intended to identify ictal and preictal states through the use of aRMT and pRMT. Context-sensitive fine-grained assessments with an excellent temporal resolution in the context of daily life are the hallmarks of RADAR Epilepsy.

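### The article claims to identify preictal states and to overcome arbitrary time windows, but both seizure models relate aggregated features to counts per unspecified window, and none is anchored on seizure onset

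*Protocol article*

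**What the plan says.** **The claim.** The abstract's Conclusions describe a framework "intended to identify ictal and preictal states through the use of aRMT and pRMT in the real-life environment". The Discussion (Principal Findings) repeats this intent. It names as a major weakness of earlier work "the choice of arbitrary time windows between the assessment of a specific factor and the consequent occurrence of a seizure", noting that the previous day is the usual choice. It adds that "Prediction might be more robust over short time frames for some precipitants and premonitory features and over long time periods for others", and then that "RADAR Epilepsy aims to overcome the current methodological issues".

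**The analysis.** The Statistical Analysis Plan looks for features that "correlate with seizure occurrence and frequency per unit of time (eg, day and week"). The predictors are "Aggregated features obtained from biosensors, smartphones, and cognitive tests and from ESM and their changes from baseline or previous time points". Two seizure models follow:
- a univariate mixed model for the number of seizures per unit of time, with participant as random effect;
- multivariate predictive models that use data aggregated over a period of unstated length to predict the seizure count over a period of equal duration.

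A separate analysis compares wearable detections with the diary (sensitivity and false alarm rate).

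**The data.** Under Study Technology, the wristband is worn throughout, the seizure diary records the time of each event, and the experience sampling method (ESM) gives 9 prompts a day for 6 days every 6 weeks.

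**The formal aim.** Aim 3 under Study Objectives is to estimate variation in seizure occurrence and in outcomes such as seizure frequency. It does not mention preictal states.

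**The concern.** A preictal state is defined by its position relative to seizure onset. Testing for one needs a comparison between the time just before onset and comparable seizure-free time. A model of seizure counts per window does not make that comparison: it asks whether windows with more seizures have different feature values. If the window is a day or a week, a change confined to the last hour or so before onset is a small part of what is aggregated.

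Leaving the window length open also leaves in place the arbitrary choice that the Discussion criticises. The Discussion expects the best window to differ between precursors, yet no comparison of lengths is described. At stake is a headline conclusion of the abstract: the study could follow its plan exactly and still have no result, positive or negative, on preictal change.

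**Working it through.** The article gives no power or sample-size figure for this question, so there is none to reproduce. The first step compares the passages; the rest are illustrations on stated assumptions.

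**1. Does any planned analysis test a preictal state?**

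| Analysis | Outcome | Anchored on onset? | Compares window lengths? |
|---|---|---|---|
| Univariate mixed model | seizures per unit of time | no | no |
| Predictive models | seizures per window | no | no |
| Wearable v diary | detection of seizures (ictal) | concerns the event itself | no |

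None does.

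**2. Dilution in a window mean.** A shift of k SD lasting L hours moves the mean of a W-hour window by k × L / W, in SDs of the raw feature. The values of k and L are assumed.
- 1 SD for 1 h: 1 × 1/24 = 0.042 (day); 1 × 1/168 = 0.006 (week). A 2 SD shift for 0.5 h gives the same.
- 2 SD for 6 h: 2 × 6/24 = 0.50 (day); 2 × 6/168 = 0.071 (week).

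**3. Allowing for the smaller noise of a mean.** A simulation with 15-minute steps, 4,000 windows per group and lag-one autocorrelation of 0 or 0.9 gave these AUCs for windows with v without the brief shift:

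| Window | 1 SD for 1 h (autocorrelation 0 / 0.9) | 2 SD for 0.5 h (0 / 0.9) |
|---|---|---|
| Matched to the change | 0.92 / 0.78 | 0.98 / 0.93 |
| 24 h | 0.60 / 0.51 | 0.62 / 0.53 |
| 168 h | 0.55 / 0.52 | 0.55 / 0.51 |

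**4. Data available.** With 32 participants, at least 2 seizures a month and 6 months, all completing: 32 × 6 × 2 = 384 seizures or more. Table 1 shows five ESM blocks, the last at the study-end visit, so 4 × 6 = 24 to 5 × 6 = 30 ESM days of 168 (14% to 18%). At the minimum rate, seizures on ESM days number 32 × 24 × 12/168 = 55 to 32 × 30 × 12/168 = 69. If half have a waking prompt just before onset (assumed), about 27 to 34 are usable; 32 is taken below.

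**5. ESM illustration over shift duration.** Assume a 0.6 SD shift in the last m of 9 prompts and a within-day correlation of 0.3. The SD of the daily mean is √(0.3 + 0.7/9) = 0.615, so the standardised effect is d = (0.6 × m/9)/0.615. Two-sided 5% power is Φ(d√32 − 1.96) + Φ(−d√32 − 1.96). Prompts are about 13.5/9 = 1.5 h apart.

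| Prompts shifted | d, daily mean | Power, daily mean |
|---|---|---|
| 1 (about 1.5 h) | 0.108 | 9% |
| 3 (about 4.5 h) | 0.325 | 45% |
| 6 (about 9 h) | 0.651 | 96% |
| 9 (whole day) | 0.976 | >99% |

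Using only the last prompt before onset, d = 0.6 and power is 92% at an uncorrected 5% level, or about 81% after Bonferroni correction for four windows (α = 0.05/4 = 0.0125). Correction across features would lower it further. The formula treats seizures as independent, the control mean as known and onset times as exact, so real power would be lower. For shifts of about 9 hours or more, the daily mean does at least as well as the single prompt.

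**The case against.** The strongest reply is that resolution has not been fixed at day or week, and that a journal article may leave window details to the full protocol or analysis plan. Much of this stands, and it rules out several stronger readings that a reader might infer.

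- **That every seizure model uses day- or week-level features.** Day and week are examples and describe the seizure outcome. The predictive window has no stated length, so shorter windows are open.
- **That one window applies to all features.** The text ties the length of the predictor window to that of the outcome window. It does not fix one length across features.
- **That short changes are necessarily averaged away.** Aggregation need not be a mean, and "their changes from baseline or previous time points (delta features) will be used for statistical analysis", which keeps some temporal change. Slow changes largely survive a daily window.
- **That formal aim 3 goes unmet.** The count models address it. The secondary outcome on the long-term trajectory of seizure frequency is likewise about frequency. The preictal wording describes the intent of a data-collection framework.
- **That a null result will be reported as no preictal change.** No passage plans that inference.
- **That the loss is 92% v 9% power.** That contrast needs a shift confined to one prompt in nine, a daily mean and no multiplicity correction.

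Event anchoring also depends on diary times entered after an evening prompt, and the abstract's Background itself calls self-reported seizures highly unreliable.

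What does not stand is that this is only an omitted detail. The article describes its seizure analyses, and their structure does not match its own Discussion. A shorter window would still give a count model that is not anchored on onset.

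**Conclusion.** The point holds as a mismatch between claim and analysis within the article. The preictal intent appears in both the abstract and the Discussion, and no analysis described tests it. The criticism of arbitrary windows is answered with a window of unspecified length and no comparison of lengths.

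The size cannot be given as one figure. On the assumed inputs, changes of about an hour or less are close to invisible in a weekly mean (AUC 0.51 to 0.55) and weak in a daily mean (0.51 to 0.62). Changes lasting many hours remain detectable at day level. These results assume mean-type aggregation; shift size, duration and correlation are not in the article.

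This affects a secondary part of the study. The primary usability and acceptability outcome is untouched. The change is worth making because the claim is a headline conclusion and the data to test it are already being collected.

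**What to change.** Add one prespecified within-participant, event-anchored analysis, for example a time-stratified case-crossover:

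- Compare sensor values, and ESM values where available, in several lead windows (for example 1, 6, 24 and 72 hours) that end before the diary- or device-timed onset.
- Take matched seizure-free control times from the same participant.
- Correct across windows and features.
- Add a sensitivity analysis for error in diary times, and use the shortest windows only where onset time is reliable.
- If power is discussed, show it over a range of assumed shift durations, as an illustration.

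Otherwise, limit the claim in the abstract and Discussion to seizure risk at the time resolution analysed.

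The cost is analysis work only, with no new data collection. The drawbacks are more tests in the multiplicity correction and dependence on the accuracy of self-reported times. ESM covers only 14% to 18% of follow-up, so most of the information would come from the continuous sensors.

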## Methods

### Study Design and Population

This study is a multicenter, prospective, observational, nonrandomized, and noninterventional cohort study in which 32 individuals with a diagnosis of epilepsy will be asked to download several RMT apps and use a wearable device for up to 6 months of follow-up. The inclusion and exclusion criteria are provided in Textboxes 1 and 2, respectively.

Inclusion criteria.Inclusion criteriaAble to give informed consent for participationDiagnosis of epilepsyAged between 18 and 70 yearsMinimum average seizure frequency of 2 seizures per monthWilling and able to complete self-reported assessments via smartphonesFluent in English (German in Freiburg) and able to read and write English (German in Freiburg)Willing to continuously wear the study wearable deviceExisting ownership of an Android smartphone (or willingness to use an Android smartphone, which will be provided as their only smartphone)Existing ownership or the possibility of connecting to a Wi-Fi connection on a daily basis

Exclusion criteria.Exclusion criteriaEstablished diagnosis of psychogenic nonepileptic attacks (dissociative seizures) as the only seizure typeFrequent vigorous involuntary movements (eg, chorea and athetosis) or frequent parasomnias with major motor components (eg, sleep walking and night terrors)Inability to comply with the trial procedure, such as cognitive or behavioral problemsInability to give informed consentUnwillingness to use an Android smartphone

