### Study Technology

The open-source RADAR-base platform [41] developed to support the RMT data collection is described elsewhere [42]. A number of variables will be collected from each patient through the RMT.

pRMT includes the following:

Smartphone app: Participants will be assisted in downloading a purpose-built app that will run in the background, requiring no further input. Using sensors commonly present in all modern smartphones, the app will collect data on ambient noise, ambient light, GPS location, bluetooth connectivity, and battery life. GPS location data will be randomized (providing relative location data, not absolute coordinates).Wearable device: Participants will be asked to wear the Empatica E4 device, a Conformitè Europëenne–marked wristband (Figure 1), for the entire duration of the study (6 months). The device will require a few hours of charging once daily, and participants will receive training and accessories to do so on a routine basis and a second E4 device to be worn during the charging procedure. The sensors included in this wearable device and the parameters measured are PPG and series of interbeat intervals derived from it, 3D acceleration, body temperature, and EDA.

A number of variables of interest to this study will be collected through a second purpose-built aRMT app, which will prompt the study participant to complete validated questionnaires and assessments according to the study schedule (Table 1):

Psychiatric comorbidities: Anxiety will be measured via the 7-item Generalized Anxiety Disorder Questionnaire [43]; depressive symptoms will be monitored via the 8-item Patient Health Questionnaire [44].

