### Study Procedures

Participants will be recruited over 6 months from the Epilepsy Service and Clinical Neurophysiology Department at King’s College Hospital, London, and from the Epilepsy Center, Department of Neurosurgery, University of Freiburg, Germany.

Potentially eligible individuals will be identified among those attending a routine outpatient appointment or hospital video–EEG EMU admission or home video–EEG monitoring appointment at the participating sites. These individuals will be approached by a member of the on-site research team and given the study information sheet and consent form.

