### Study Outcomes

The primary outcome of interest was participants’ acceptability and usability of the RADAR technology, including the wearable, the apps, and the assessment scheme. Acceptability and usability will be evaluated using the Post-Study System Usability Questionnaire (PSSUQ) [46]; the Technology Assessment Model Fast Form (TAM-FF) [47]; and ad hoc created qualitative interviews undertaken at 1, 3, and 6 months postenrollment. Participants who dropped out before the study endpoint will be contacted to complete an interview.

Secondary outcomes include (1) sensitivity and false alarm rate of the device, as compared with patient seizure diary, for different seizure types: generalized tonic-clonic seizures, focal seizures (FS) with motor features, FS with autonomic features, and FS with dyscognitive features and (2) identification of variables influencing the long-term trajectory of seizure frequency: pRMT features (measured through the wearable sensors and smartphone sensors), and aRMT assessments, including comorbidities, seizure precipitants, ESM, speech, and cognitive functions.

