### Statistical Analysis Plan

Descriptive statistics for demographics, attrition rate, and number of participants using remote assessment measurements will be estimated. The primary outcome measurement (PSSUQ and TAM-FF) will be analyzed using a mixed-effect model for repeated measures based on observed case data. The model will include the duration in the study and contextual variables (CSRI, LTE-Q, etc) as covariates. Using classification approaches, we will investigate whether any demographics and/or other numerical information might serve as a predictor for subjects dropout. Using mixed-effect models with participants as a random factor, we will estimate whether there is a univariate relationship between the amount of RMT usable data during the weeks before the outcome assessment and obtained scale measurements (PSSUQ and TAM-FF). Acoustic features such as pitch, jitter, shimmer, formants, and intensity of the voice will be extracted from the speech task and will be analyzed.

To assess seizure detection performance of a multiparametric wearable system, we will relate seizures detected by the wearable system to the information from the seizure diary, kept by each participant. We will estimate the sensitivity of seizure detection by the wearable system (ie, whether all seizures reported in the diary were detected by wearable system) and false alarm rate (ie, number of seizures detected by the wearable system but not reported in the diary per unit of time, eg, day).

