## Results

The RADAR-CNS project has received funding in 2015 from the Innovative Medicines Initiative 2 Joint Undertaking under Grant Agreement No. 115902. This Joint Undertaking receives support from the European Union’s Horizon 2020 research and innovation program and European Federation of Pharmaceutical Industries and Associations (EFPIA). Ethical approval was obtained in London from the Bromley Research Ethics Committee (REC reference: 19/LO/1884) in January 2020. The first study participant was enrolled on September 30, 2020. Data will be collected until September 30, 2021. The results of the study are expected to be published at the beginning of 2022.

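### The univariate seizure-frequency model has no time-in-study term, so a feature that shares only a time trend with seizure counts can look like a correlate

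*Protocol article*

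**What the plan says.** One of the secondary outcomes (Study Outcomes) is "identification of variables influencing the long-term trajectory of seizure frequency". For the first analysis step, the Statistical Analysis Plan section states: "number of seizures per unit of time will be modeled with each variable or feature as a fixed effect and participant as a random effect". The only further terms it names are demographics and other baseline characteristics, to be used where needed. Features enter as levels and as changes from baseline or from the previous time point. A correction for multiple comparisons is planned.

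The same section treats the usability questionnaires differently: "The model will include the duration in the study and contextual variables", the latter including health service use and life events.

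Follow-up and calendar: participants "use a wearable device for up to 6 months of follow-up"; "Participants will be recruited over 6 months"; and, in Results, "The first study participant was enrolled on September 30, 2020. Data will be collected until September 30, 2021". The smartphone app records, among other things, "ambient noise, ambient light, GPS location". Study Monitoring adds that incoming data will be used to change the software and the questionnaire schedule while the study runs.

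**The concern.** A participant effect removes differences between people. It does not remove a movement that the cohort shares over follow-up, and covariates fixed at baseline cannot remove it either. The stated model therefore cannot separate a feature that goes with seizures week by week from one that has only the same time course.

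The design offers plausible sources of a shared time course on both sides, although the document quantifies none:

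- Counts: a nightly diary kept for about 24 weeks may be filled in less over time. Seizures derived from the wearable may be detected less often if wear falls.
- Features: wear and app use may change, repeated cognitive tests may show practice effects, and light and mobility can follow the season.
- Both: changes to the platform or questionnaires during the study may alter how either is recorded.

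At stake is the list of variables reported as influencing seizure frequency. The error is bias, so adjusting p-values for the number of features tested does not remove it.

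**Working it through.** The document gives no error rate, power or trend for this model, so there is no stated figure to reproduce. The check asks what the stated model does to a feature with no relation to seizures.

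**Inputs from the document.** N = 32 participants (Study Design and Population); 24 weeks of follow-up (Table 1), taken as W = 24 weekly counts.

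**Assumptions.** Poisson counts; median 0.7 seizures per week; between-person log SD 0.6; a common log-linear fall in counts of d over follow-up; a feature with within-person SD 1 that drifts linearly by D SD; two-sided 5% test; participant intercept conditioned out, standing in for the participant effect.

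**Approximation.** Scale time t from 0 to 1.

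- Variance of 24 equally spaced points: V = (W + 1) / [12(W − 1)] = 25/276 = 0.0906.
- Log slope of counts: g = ln(1 − d).
- Spurious coefficient when time is omitted: b ≈ g·D·V / (1 + D²V).
- Mean weekly rate at start: 0.7 × exp(0.6²/2) = 0.838. Expected total count: M = 32 × 24 × 0.838 × d/(−g) = 643.6 × d/(−g).
- SE ≈ 1/√[M(1 + D²V)], and z = |b|/SE.
- False-positive rate ≈ Φ(z − 1.96) + Φ(−z − 1.96).

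**Example, d = 30%, D = 2.** g = −0.357; M = 643.6 × 0.841 = 541; 1 + D²V = 1.362. Then b = −0.357 × 2 × 0.0906/1.362 = −0.047, SE = 1/√(541 × 1.362) = 0.037, z = 1.29. The rate is Φ(−0.67) + Φ(−3.25) = 25%.

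**All settings**, with simulation under the same assumptions (1500 runs each):

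| Fall in counts | Drift (SD) | z | Formula | Simulated, no time term | Simulated, week term |
|---|---|---|---|---|---|
| 20% | 1 | 0.47 | 8% | 7% | 4–6% |
| 20% | 2 | 0.83 | 13% | 13% | 4–6% |
| 30% | 1 | 0.72 | 11% | 12% | 4–6% |
| 30% | 2 | 1.29 | 25% | 25% | 4–6% |
| 50% | 1 | 1.30 | 25% | 26% | 4–6% |
| 50% | 2 | 2.32 | 64% | 65% | 4–6% |

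**Only one side trends.** The coefficient contains the product g·D, so it is zero if either is zero. Simulated rates then stay at about 4 to 7%.

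**Higher seizure rate.** With 26 weeks and a mean starting rate of about 1.4 per week, the rates without a time term for drifts of 1 and 2 SD are 11% and 22% (20% fall), 16% and 40% (30%), and 40% and 87% (50%). With a week term they are about 4 to 7%.

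**Delta features.** Change from baseline is the level minus one constant per participant. In these fits the participant intercept absorbs that constant, so the rates equal those for levels. Change from the previous time point turns a linear drift into a constant, D/23 per week, which leaves no trend to share with the counts; its simulated rate is 4 to 6% in every setting.

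**Calendar.** 30 September 2020 plus 24 weeks is 17 March 2021. A participant entering six months later, on 30 March 2021, reaches 24 weeks on 14 September 2021. Each person is seen for about half a year, but entry is staggered, so calendar time and time in study can be estimated separately across the cohort.

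**The case against.** The strongest reply is that this is an exploratory analysis of a secondary outcome, in an article that condenses a fuller plan, and that a complete covariate list may stand there. That carries weight for anything the article leaves open. It carries less here, because the article writes this model out, names the covariates it may take, and in the same section gives the usability model a time term.

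Second, the document shows no trend in seizures or in any feature, and the mildest assumed case gives 7%, barely above nominal. This stands: the size is conditional on assumed trends.

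A reader might also infer more than the document supports:

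- *That any drifting feature will be flagged.* The counts must trend as well.
- *That entry on a minimum seizure frequency makes counts fall during follow-up.* Selection on past frequency mainly gives a step at entry. With an assumed 3-month look-back and stable individual rates it is about 3 to 10%, and it comes before the first modelled week.
- *That delta features are the worst affected.* Change from baseline behaves like the level, and change from the previous time point is largely protected.
- *That season and time in study move together within every participant.* Someone followed from October to mid-March passes through midwinter, so light falls and then rises.
- *That the multivariate prediction models also omit time.* Their candidate terms are not listed, so this cannot be said.

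**Conclusion.** The point holds for the univariate seizure model. As written it has no term for time in study, although its outcome is a trajectory and the usability model has such a term. Where counts or their recording and a feature both trend across the cohort, the 5% error for an unrelated feature rises to about 7 to 65% under the assumed falls and drifts, and to as much as 87% at the higher assumed seizure rate. A linear week term brings it back to about 4 to 6% (4 to 7% at the higher rate). Without a trend on both sides there is no inflation. These figures rest on Poisson counts, linear trends common to all participants, and rates, falls and drifts that are not in the document. The point concerns level and change-from-baseline features. It should be corrected before analysis, but it does not touch the primary usability outcome.

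**What to change.** In the Statistical Analysis Plan section, add time in study (linear, or a low-order spline) as a fixed covariate in every univariate seizure model. Do this for diary-derived and wearable-derived counts alike. Add calendar month or season as a further covariate or as a sensitivity analysis; staggered entry makes both estimable. Report each feature's estimate with and without time, so that readers can see which associations rest on a shared time course. A common time term removes only the trend that participants share, so participant-specific trends are a reasonable sensitivity analysis.

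The change is to wording only, since the dates are already recorded. The cost is lower power for a feature whose only link with seizures is a slow drift, and the plan should say so.

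### The univariate seizure screen names no allowance for serial dependence or for slopes that differ between participants, so its p-values can be too small when seizure rate and feature are both persistent

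*Protocol article*

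**What the plan says.** The protocol article (Methods, Statistical Analysis Plan, paragraph on multi-sensor data) asks which features "correlate with seizure occurrence and frequency per unit of time (eg, day and week"). The first step is described in these words: "number of seizures per unit of time will be modeled with each variable or feature as a fixed effect and participant as a random effect". One further sentence governs what else may enter: "Demographics and other baseline characteristics will be added to the model when necessary". On repeated testing it says: "Correction for multiple comparisons will be taken into account". The features are aggregated levels and "their changes from baseline or previous time points (delta features) will be used for statistical analysis".

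Study Design and Population fixes the amount of data. On numbers it says: "32 individuals with a diagnosis of epilepsy will be asked to download several RMT apps". On duration, participants are to "use a wearable device for up to 6 months of follow-up". Table 1 runs for 24 weeks.

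The section names no count distribution, significance level, serial-correlation term, random slope or variance estimator for this step. It also does not say that any of these is excluded.

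**The concern.** A model with one feature slope and one participant effect supplies a p-value for a compound null: no association, days or weeks independent given the participant's level, and the same slope in everyone. Rejecting that null is not the same as finding a correlate.

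The article itself gives reason to doubt the second part. Its second secondary outcome is the long-term trajectory of seizure frequency, so a rate that changes within a person is part of the question. The Discussion adds that some factors may predict over long periods. Sleep, mood and activity levels may well persist from day to day too. When two unrelated series both drift slowly, they line up by chance more often than independent rows allow. Demographics and baseline characteristics cannot absorb this, because they do not vary within a participant.

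At stake is the list of features reported as related to seizure frequency (aim 3 and the second secondary outcome). A multiplicity correction takes each p-value as valid, so it cannot repair p-values that are already too small.

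**Working it through.** **Inputs from the article.** 32 participants; 24 weeks, or 168 days; at least 2 seizures per month. This gives 32 × 168 = 5,376 daily rows, 32 × 24 = 768 weekly rows and, at the floor rate, 32 × 6 × 2 = 384 seizures. The article states no error rate for this step, so there is no figure to reproduce.

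**Assumptions (not in the article).** Two-sided 5%; Poisson counts; mean rate r of 2, 4 or 10 per month; between-participant log-rate SD 0.7; within-participant log-rate following a first-order autoregression with SD σ and day-to-day correlation φ; an unrelated feature with day-to-day correlation ρ.

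**Formula.** For daily rows, the ratio of the true variance of the test's score to the variance the model assumes is approximately

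V = 1 + m × [(e^(σ²) − 1) + 2 × Σₖ ρᵏ (e^(σ²φᵏ) − 1)], with m = (r/28) × e^(0.49).

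The first term in the bracket is overdispersion and the second is serial dependence. The second vanishes if the feature has no autocorrelation (ρ = 0). The rejection rate is 2Φ(−1.96/√V).

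- **Strong dependence** (φ = ρ = 0.9, σ = 1): the bracket is 1.718 + 2 × 5.997 = 13.71. At 2 per month, m = 0.117, V = 2.60 and 1.96/√V = 1.216, giving 22%. At 10 per month, m = 0.583 and V = 8.99, giving 51%.
- **Mild dependence** (φ = ρ = 0.5, σ = 0.7): the bracket is 0.632 + 2 × 0.182 = 0.996. At 2 per month V = 1.12, giving 6.4%. At 10 per month V = 1.58, giving 11.9%.

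**Simulation** (1,500 data sets per cell, daily rows, unrelated feature; rejection at 2 / 4 / 10 seizures per month):

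| Feature corr. / rate corr., log-rate SD | Poisson | Overdispersion-scaled |
|---|---|---|
| No dependence in rate | 4–5% | 4 / 5 / 5% |
| 0 / 0.9, SD 1 | 6.5 / 10.3 / 14.4% | 6 / 8 / 7% |
| 0.5 / 0.5, SD 0.7 | 6.8 / 8.0 / 12.5% | 6 / 6 / 9% |
| 0.9 / 0.9, SD 0.7 | 12 / 19 / 33% | 11 / 18 / 26% |
| 0.9 / 0.9, SD 1 | 21 / 31 / 50% | 20 / 28 / 38% |
| 0.97 / 0.97, SD 1 | 33 / 45 / 59% | 31 / 44 / 55% |

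The formula and the simulation agree closely. A random-intercept Poisson likelihood-ratio test, spot-checked on 200 data sets, gave 3.5% with no dependence. At 0.9 / 0.9 with SD 1 it gave 16% at 2 per month and 34% at 4 per month. Weekly rows at 0.9 / 0.9, SD 1, gave 22 / 37 / 52% (Poisson), 16 / 18 / 23% (scaled) and 10.5–12% (linear model).

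**By type of feature** (separate runs, 2–10 seizures per month, log-rate SD 0.8, daily, Poisson / scaled):
- Level at correlation 0.9: 21 / 19%, and 21/5 is about 4 times nominal. At 0.7: 10 / 7%. At 0.5: 9 / 6%.
- Change from baseline at 0.9: 22 / 19%. Subtracting a constant leaves the within-person autocorrelation unchanged.
- Change from the previous day: about 6 / 4%.
- A 2-weekly scale (PHQ-8 in Table 1), if spread over daily rows: 22 / 18%. A 6-weekly measure (cognition), if so spread: 29 / 26%.

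With a smaller log-rate SD of 0.5, correlations of 0.7–0.9 gave only 7–8%.

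**Slopes differing around a zero mean, no serial dependence** (daily, Poisson, 2 / 4 / 10 per month): slope SD 0.1 gives 6 / 10 / 18%; slope SD 0.3 gives 29 / 41 / 58%. These are rejections of a zero average slope.

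**Multiplicity.** For illustration only, 20 unrelated features with Bonferroni correction (correlation 0.9, SD 0.8) gave a family-wise error of 58%, against 7% with clustered standard errors. The article states neither the number of features nor the correction.

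**After the change.** Participant-clustered variance with t on 31 degrees of freedom gave about 5–10% across the main simulation, with 8–10% in the slowest-drift cells. Circular-shift permutation within participants stayed near or below nominal, up to about 7%, where it was tried.

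**The case against.** The best defence is that this is a condensed article. Naming participant as a random effect does not rule out a random slope or a residual correlation structure, and covariance details often sit in a full analysis plan. The step is also a secondary, exploratory screen, followed by prediction models with cross-validation.

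Much of this stands, and it rules out several stronger readings that a reader might infer:

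- **That the plan permits only a participant effect.** It is silent on other structure; it does not forbid it.
- **That unrelated features will be declared correlates several times too often.** This needs strong persistence in both series, which the article does not quantify. Dependence in the seizure rate alone has little effect unless overdispersion is also left unmodelled.
- **That differing slopes make an unrelated feature look related.** They do not. A feature with real but opposite effects in different people is not unrelated to seizures.
- **That PHQ-8 will be carried across daily rows.** No such procedure is stated, and day and week are given only as examples.

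What remains is that the article does name a concrete model, and the only additions it names cannot deal with dependence within a person. Cross-validation is described for the later prediction models and does not check the univariate claims.

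**Conclusion.** The point holds in conditional form. Followed as written, the univariate screen can be anti-conservative. Under the assumptions above, the Poisson false-positive rate is about nominal with no or weak dependence, about 1.5 to 3 times nominal at day-to-day correlation 0.5–0.7, and about 4 times or more at 0.9 with a log-rate SD of 0.8 or above. It exceeds 10 times only in the most persistent, high-rate settings. Levels and change from baseline are exposed, as are infrequently measured scales if spread over finer rows. Change from the previous day is largely protected. An overdispersion-scaled or linear model reduces the excess but does not remove it under strong dependence.

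The slope issue is separate: a common-slope model overstates the evidence for a non-zero average effect when effects differ between people. Neither issue touches the primary outcome of acceptability and usability.

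**What to change.** In the Statistical Analysis Plan, keep the participant random effect and add:

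1. Inference for each feature is based on participant-clustered standard errors with a small-sample correction (t on about n − 1 degrees of freedom, 31 for 32 participants), or on circular-shift permutation of the feature series within each participant.
2. A participant random slope for the feature is included wherever an average effect is claimed.
3. The multiple-comparison correction is applied to those p-values.
4. Each feature is analysed at no finer time unit than the one at which it is measured.

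This takes a few sentences and a few lines of code, with no new data. The cost is wider intervals and fewer features declared significant. With 32 clusters, a small residual inflation may remain under very slow drift.
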